#### Power

For H1 examining the effectiveness of SRP + TBRI compared to SRP alone, the proposed Intent to Treat (ITT) sample will include 360 youth/safe adult dyads (120 SRP, 240 TBRI), with 80 randomized to each TBRI condition. SAS PROC POWER for rank tests comparing 2 survival curves found that, if overall opioid initiation rates are 35% (SRP) vs. 25% (all TBRI groups) at any assessed time point, power is estimated to be at 93% (*α* = .05). For H2 comparing the 3 TBRI conditions, SAS PROC POWER for rank tests comparing 2 survival curves found that for sample sizes of 80 in each group, power = .80 when the hazard ratio = 1.57. When the combined TBRI groups are tested against SRP, power = .80 when the hazard ratio = 1.37.

For H3 and H4 pertinent to the organizational TBRI intervention, the expected sample (nine sites, up to 90 staff participants per site) and the response rate of 25% gives an expected sample of 203 participants. A small effect size (0.20), a power of 0.80, significance level of 0.05, and an intraclass correlation of 0.10 are used to calculate the minimum required sample size. Repeated measures design comparing staff participants over time results in a minimum sample size of 43 participants. To be more conservative, the same parameters are used for a mixed-effect design (four repeated measures by nine sites), yielding a minimum sample size of 189 participants.

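### The 93% power stated for H1 does not follow from the rates and sample sizes printed beside it, which give about 50%; the detectable hazard ratios of 1.37 and 1.57 need nearly every youth to initiate

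*Protocol article*

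**What the plan says.** All of this stands in the Power section of the protocol article.

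- **Sample:** "360 youth/safe adult dyads (120 SRP, 240 TBRI), with 80 randomized to each TBRI condition".
- **Method:** "SAS PROC POWER for rank tests comparing 2 survival curves", at alpha .05. Sidedness, accrual, follow-up time and dropout are not given for the calculation.
- **Assumed effect for H1:** "if overall opioid initiation rates are 35% (SRP) vs. 25% (all TBRI groups) at any assessed time point".
- **Result for H1:** "35% (SRP) vs. 25% (all TBRI groups) at any assessed time point, power is estimated to be at 93" per cent.
- **Detectable effect for H2:** "for sample sizes of 80 in each group, power = .80 when the hazard ratio = 1.57".
- **Detectable effect for H1:** "When the combined TBRI groups are tested against SRP, power = .80 when the hazard ratio = 1.37".

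Elsewhere, the measurement section makes days to first non-medical opioid use the primary outcome. The effectiveness-trial section sets follow-up at 3, 6, 12 and 18 months after baseline.

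**The concern.** The power of a log-rank test depends on the number of events, not the number of youth. If roughly a quarter to a third of 360 youth initiate, there are about 100 events. A hazard ratio near 1.5 cannot give 93% power on that many.

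H1 is the first primary hypothesis. On the printed inputs, a true reduction from 35% to 25% would be missed about half the time, while the reader is told the risk is 7%. A reader who relies on 93% could take a non-significant H1 as good evidence that a 10-point benefit is absent, when the design cannot support that. The two detectable hazard ratios would mislead in the same direction.

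**Working it through.** **Inputs (Power section):** 120 and 240 dyads (allocation 1/3 and 2/3); initiation 35% and 25%; alpha .05, taken as two-sided because sidedness is not stated, with one-sided also tried. No attrition, clustering or multiplicity adjustment is applied.

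**1. Hazard ratio (SRP over TBRI, constant hazards).** ln(0.65)/ln(0.75) = 0.4308/0.2877 = 1.497; its log is 0.4037.

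**2. Events.** 120 × 0.35 + 240 × 0.25 = 42 + 60 = 102.

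**3. Trying to reproduce 93% (Schoenfeld).** Power = Φ(√(events × 1/3 × 2/3) × ln HR − z).
- Two-sided: √(102 × 2/9) × 0.4037 = 4.761 × 0.4037 = 1.92; Φ(1.92 − 1.96) = 48.5%.
- One-sided: Φ(1.92 − 1.645) = 61%.

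**4. Other methods, same inputs.**

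| Method | Two-sided power |
|---|---|
| Schoenfeld | 48.5% |
| Arcsine | 49.9% |
| Two proportions | 51.0% |
| Simulated log-rank, 20,000 runs | 52.0% |
| Lakatos-type log-rank | 52.4% |

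Freedman's approximation, which under 1:2 allocation depends on the arm taken as reference, gives 42.8% or 52.8%. One-sided, the Schoenfeld, arcsine, two-proportion and Lakatos figures run from 61% to 65%.

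**5. Events needed for 93%.** (1.960 + 1.476)² / (0.4037² × 2/9) = 326, against 102 expected.

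**6. Other readings of the time phrase.** Each applies 35%/25% to a shorter period and runs the same hazards for m such periods.

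| Reading | Cumulative initiation, SRP / TBRI | Events | Two-sided power (Schoenfeld / Lakatos) |
|---|---|---|---|
| By month 18 (m = 1) | 35% / 25% | 102 | 48.5% / 52.4% |
| In each of four intervals, treated as equal (m = 4) | 82% / 68% | 263 | 87.0% / 88.9% |
| By month 3, run to month 18 (m = 6) | 92% / 82% | 308 | 91.6% / 92.6% |

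The last row: 1 − 0.65⁶ = 0.925 and 1 − 0.75⁶ = 0.822. The four-interval reading also comes near 93% if the test is made one-sided (92.5% / 93.8%), but it too has a large majority initiating.

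**7. Detectable hazard ratios at 80% power, two-sided.** (1.960 + 0.842)² = 7.849.
- HR 1.37, 1:2 allocation: 7.849 / (0.3148² × 2/9) ≈ 356 events of 360 youth.
- HR 1.57, 80 against 80: 7.849 / (0.4511² × 1/4) ≈ 154 events of 160 youth.
- With 102 events, power at HR 1.37 is Φ(4.761 × 0.3148 − 1.96) = 32%, and the HR detectable with 80% power is exp(2.802/4.761) = 1.80.
- For an H2 pair at 25% initiation (160 × 0.25 = 40 events), power at HR 1.57 is Φ(√10 × 0.4511 − 1.96) = 30%, and the detectable HR is exp(2.802/√10) = 2.4.
- If all 360 youth had events, HR 1.497 would have Φ(√80 × 0.4037 − 1.96) = 95% power.

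**8. What 80% power would need.** With SRP at 35% and TBRI at 20.7%: 42 + 49.7 = 91.7 events, HR 0.4308/0.2319 = 1.86, power Φ(4.514 × 0.619 − 1.96) = 80%. At 21% the HR is 1.83 and power is 78% by Schoenfeld and 81% by two proportions. So about 35% against 21%, HR about 1.8.

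**The case against.** The best defence is that the time phrase is loose and 93% can be recovered. If 35% and 25% are taken as the rates at the month-3 assessment and the hazards continue unchanged to month 18, the Lakatos-type calculation gives 92.6%, in effect the printed figure. A time input entered or described wrongly is therefore a plausible origin. It would be going too far to say that no reading gives 93%.

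This explains the number but does not support the sentence. The Power section calls these overall initiation rates, and the month-3 reading would have about 92% and 82% initiating. The effectiveness-trial section also places the month-3 interview within two weeks of discharge, after baseline 2–3 months before it. A month-3 rate would thus be mostly time in the secure facility, whereas H1 concerns initiation after discharge.

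It is also fair that a condensed article may leave sidedness, accrual and follow-up time to the full protocol, so what was entered in the software cannot be known. That limits any claim about the cause. It does not help the figure, since a one-sided test at the printed overall rates gives at most about 65%.

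A reader might infer that the Sidak adjustment in the data analysis plan pushes H1 power far below 50%. The article does not define the family of tests, which might cover only the H2 pairs, so no adjusted figure is used here.

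**Conclusion.** The point stands as an inconsistency within one paragraph. At the printed overall rates and sample sizes, two-sided power for H1 is about 50%, so the stated 93% is more than 40 percentage points too high. The 1.37 and 1.57 hazard ratios share the same feature: they fit only if almost every youth initiates. That suggests a common problem with the event count, though the documents do not show how it arose.

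The result assumes roughly constant hazards, a two-sided test and no attrition; loss to follow-up would be expected to lower power further. A reader might infer that the trial must enrol more or that the H1 analysis is invalid. The documents do not support either: the endpoint, the test and the estimate are unaffected. What changes is the stated power and how a non-significant H1 may be read.

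**What to change.** Re-run all three figures on one stated overall event rate, follow-up time and sidedness. Correcting only the 93% would leave HR 1.37 beside a detectable HR of about 1.8 for the same comparison.

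If 35% against 25% overall is meant:
- state that 120 against 240 dyads give about 102 events (HR 1.50) and about 50% power at two-sided alpha .05, and that 80% power needs about 35% against 21% (HR about 1.8);
- replace HR 1.37 and HR 1.57 with values consistent with that event rate (for an H2 pair with 40 events, about 2.4);
- add that a non-significant H1 does not rule out a 10-point effect, so the estimate and its confidence interval carry the conclusion.

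If month-3 rates were meant, say so and state the implied 18-month cumulative rates.

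The cost is three short power calculations and a rewritten paragraph, with a less favourable stated power. Enrolment, design and conduct do not change.

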## Methods/design

### Research aims

The specific aims of the LeSA Project are to: (1) test the effectiveness of the TBRI intervention and its different support formats – no in-home TBRI support, Structured Coaching, Responsive Coaching – on (a) preventing initiation and/or escalation of opioid use, (b) public health and public safety outcomes, (c) putative change mechanisms, including self-regulation, psychosocial functioning, and relationship with a safe adult; (2) document factors related to TBRI implementation and sustainment; and (3) estimate the start-up and implementation costs and cost-effectiveness of TBRI support options relative to standard re-entry practices in achieving lower rates of opioid initiation and reductions in healthcare and JJ system costs.

Primary hypotheses are as follows:
H1: Compared to youth receiving Standard Re-entry Practices (SRP) only, youth receiving TBRI in addition to SRP are less likely to initiate opioid use following discharge.H2: Compared to no in-home TBRI support, youth receiving Structured or Responsive Coaching are less likely to initiate opioid use following discharge, with the longest time to initiation occurring among youth receiving Responsive Coaching.H3: TBRI is most effective for preventing opioid initiation when facilities routinely use TBRI strategies within their residential settings, given increases in continuity as the youth transitions home from residential care.H4: The cost of implementing TBRI + SRP is higher than SRP alone, with higher cost-effectiveness when TBRI is added.

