### Data analysis plan

For all analyses, an ITT approach is used, where all study participants are included in analyses. For H1 and H2, comparisons of survival curves for each group are performed using SAS PROC PHREG and PROC GLIMMIX using the log rank test with the Sidak multiple-comparison adjustment, with the primary outcome as the dependent variable. Differences between groups on secondary outcomes and change over time in implementation measures (e.g., TBRI use) are examined using repeated measures ANOVAs (SAS 9.4, PROC MIXED), with study site as random effects and condition, time, and interactions as fixed factors. Because SU rates are generally lower among JJ females, sex as a biological variable is examined as a moderator of differences in outcomes using univariate analyses (e.g., chi square, t-tests, ANOVA); when significant, tests of moderation are undertaken as part of all analyses. Putative change mechanisms are investigated as mediators of the Group – Primary Outcome relationship and structural equation modeling (SEM; using Mplus) is used to examine sex differences in mediation. For H3, changes in the outcomes over time are examined using repeated measures ANOVAs (SAS 9.4, PROC MIXED), with study site as random effects and time and time × site interactions as fixed factors. For H1–3, a log rank test is used to assess study dropout; stochastic multiple-imputation provides maximum likelihood estimates, accounts for uncertainty in missing values, and provides unbiased estimates of the treatment effect if data are missing at random.

Qualitative data from focus groups are transcribed and qualitatively coded (in Atlas.ti) by at least 2 research staff. An iterative process of coding and thematic analysis [84] are used to understand routine practices employed, nuances in the use of trauma-informed and child-centered strategies, facility facilitators/barriers to uptake of new interventions, general penetration of TBRI within the facility, and facility interest in sustaining and/or expanding TBRI practices.

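### The hazard ratios quoted for 80% power (1.57 for H2, 1.37 for pooled TBRI vs SRP) require virtually every youth to initiate opioids and leave out the planned Sidak adjustment

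*Protocol article*

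**What the plan says.** The Power section sets the sample at "360 youth/safe adult dyads (120 SRP, 240 TBRI), with 80 randomized to each TBRI condition". It then makes three power statements, based on "SAS PROC POWER for rank tests comparing 2 survival curves":

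- H1: 93% power at alpha .05, "if overall opioid initiation rates are 35% (SRP) vs. 25% (all TBRI groups) at any assessed time point".
- H2: "for sample sizes of 80 in each group, power = .80 when the hazard ratio = 1.57".
- Pooled contrast: "When the combined TBRI groups are tested against SRP, power = .80 when the hazard ratio = 1.37".

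No event rate is attached to the second and third statements. The only initiation rates in the document are the 35% and 25% of the H1 statement, and the 25% is given for all TBRI groups, which are the groups that H2 compares.

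The Data analysis plan section says that the H1 and H2 survival curves are compared "using the log rank test with the Sidak multiple-comparison adjustment". The Power section does not mention that adjustment. H2 itself (Research aims) involves all three formats: either coaching format against no in-home support, "with the longest time to initiation occurring among youth receiving Responsive Coaching".

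**The concern.** A log-rank test draws its power from the number of initiations observed, not from the number of dyads enrolled. With 80 youth per arm and about a quarter initiating, a hazard ratio of 1.57 looks far too small to be detected with 80% power. The two quoted hazard ratios look like the output of a calculation in which every youth has the event and no multiplicity adjustment is made.

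The stake is greatest for H2. The SRP youth are recruited in an earlier stage at the same sites and are not randomised against TBRI, so the three support formats form the only randomised comparison. A reader of the Power section would conclude that 80 per arm can detect a moderate difference between formats. A non-significant H2 result could then be taken as evidence that coaching adds nothing. The cost-effectiveness comparison between support conditions rests on the same contrasts.

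**Working it through.** **Inputs.** Arms of 80 (160 per H2 pair); 120 SRP and 240 TBRI for the pooled contrast; initiation 25% (TBRI) and 35% (SRP); alpha .05 (all from Power); Sidak adjustment (Data analysis plan). Assumed: two-sided tests, because sidedness is not stated; the rates read as cumulative over follow-up; three pairwise comparisons in the H2 Sidak family, because its size is not stated.

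**Formula (Schoenfeld).** With D events and a fraction p in one arm, power = Φ(√(D·p(1−p))·|ln HR| − z₁₋α/₂). The hazard ratio for 80% power is exp((z₁₋α/₂ + 0.84)/√(D·p(1−p))). At two-sided .05 the numerator is 1.96 + 0.84 = 2.80.

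**Step 1: reproduce the quoted figures.** Set events equal to youth.
- H2, D = 160, p = 1/2: √40 × ln 1.57 = 6.325 × 0.451 = 2.85; power .814. The hazard ratio for exactly 80% is 1.557. The events needed at 1.57 are 155 (Schoenfeld) or 160 (Freedman), out of 160 youth.
- Pooled, D = 360, p = 1/3: √80 × ln 1.37 = 8.944 × 0.315 = 2.82; power .804. The hazard ratio for exactly 80% is 1.368. The events needed at 1.37 are 357 of 360.
- A Lakatos-type log-rank calculation with all events gives .802 and .799.

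Both figures therefore match an all-events calculation at unadjusted two-sided .05.

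**Step 2: can the Sidak adjustment be inside the H2 figure?** For three comparisons the per-test alpha is 1 − 0.95^(1/3) = .01695. With all 160 youth initiating, power at 1.57 is only .68, and 206 events would be needed from 160 youth. For two comparisons (alpha .0253) it is .73. The H2 figure therefore cannot include the adjustment.

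**Step 3: use the document's own rates.**
- Events per H2 pair: 0.25 × 160 = 40.
- Events, pooled: 0.35 × 120 + 0.25 × 240 = 42 + 60 = 102.

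| Contrast | Events | Alpha | Power at quoted HR | HR for 80% power |
|---|---|---|---|---|
| H2 pair (1.57) | 40 | .05 | 30% | exp(2.80/√10) = 2.43 |
| H2 pair (1.57) | 40 | .01695 | 17% | 2.78 |
| TBRI vs SRP (1.37) | 102 | .05 | 32% | exp(2.80/4.761) = 1.80 |

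Under proportional hazards and an average of 25%, a hazard ratio of about 2.4 corresponds to roughly 34% vs 16% initiating (ln 0.66/ln 0.84 = 2.38), and 2.8 to about 35.5% vs 14.5% (ln 0.645/ln 0.855 = 2.80).

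**Step 4: sensitivity of H2 to the rate (two-sided, unadjusted).** At 35% initiation in every TBRI arm (56 events), power at 1.57 is 39% and the detectable hazard ratio is 2.11. At 50% (80 events), √20 × 0.451 = 2.02 and power is 52%.

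**Step 5: one-sided .05.** The quoted hazard ratios would still need 122 of 160 (76%) and 281 of 360 (78%) youth to initiate. The all-events hazard ratios would be 1.48 and 1.32, which do not match the quoted ones.

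**The case against.** The strongest objection concerns the rates. They stand in the H1 sentence and are described as holding at any assessed time point, not cumulatively over 18 months. If they applied afresh at each of the four follow-ups, cumulative initiation would be 1 − 0.65⁴ = 82% (SRP) and 1 − 0.75⁴ = 68% (TBRI), giving about 109 events per H2 pair and 263 pooled. Power at 1.57 would be about 65% (49% with Sidak for three comparisons) and the detectable hazard ratio about 1.71 (1.85 with Sidak). Pooled, 1.37 would have about 67% power and 80% would need about 1.44. This reading sits badly with the word overall in the same sentence, and the quoted figures still fail under it. What stands is that the size of the shortfall depends on the reading, so the assumption must be stated.

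Two smaller points also stand. Strictly, the requirement is 97–100% of youth, not every single one. The Sidak family size is not given and may be set in an analysis plan that is not shown, so the .017, 17% and 2.8 figures are conditional on three comparisons; with two, the detectable hazard ratio at 40 events is 2.65. The adjustment is clearest for H2. For the pooled contrast it depends on whether that test belongs to the adjusted family.

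It may also be said that nothing in the conduct of the trial changes and that an article condenses its protocol. But the issue is not an omission: the article prints specific figures that conflict with the rates in the same paragraph.

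**Conclusion.** The concern holds: both power statements are wrong as written. The quoted hazard ratios describe a trial in which virtually every youth initiates opioid use and H2 is tested without adjustment. On the document's own rates, read as cumulative, power at those hazard ratios is about 30% for an H2 pair (17% with Sidak for three comparisons) and 32% for TBRI against SRP, instead of 80%. The effects detectable with 80% power are hazard ratios of about 2.4 (2.8 with Sidak) and 1.8. The per-visit reading narrows the gap but does not close it. Because H2 is a primary hypothesis and the only randomised comparison, the text needs correcting. The exact sizes rest on two-sided tests, proportional hazards, the stated 25% and 35%, and the assumed Sidak family.

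**What to change.** Replace the two hazard-ratio statements with detectable effects derived from expected events:

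- H2 pairwise: about 40 events at 25% initiation; 80% power for a hazard ratio of about 2.4 at two-sided .05, or about 2.8 with Sidak for three comparisons.
- TBRI against SRP: 102 expected events; 80% power for a hazard ratio of about 1.8 at two-sided .05.

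State with them whether the 35% and 25% are cumulative over follow-up, whether tests are one- or two-sided, and which comparisons form the Sidak family. If a higher initiation rate is expected, give it and recompute.

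Reconcile the 93% for H1 in the same rewrite. As cumulative rates, 35% vs 25% is a hazard ratio of ln 0.65/ln 0.75 = 1.50, which has about 48% power at 102 events (two-sided). Left alone, the text would claim 93% power at 1.50 beside 80% power at 1.80 for the same test.

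The cost is rewording; no sample size or procedure changes.

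Optionally, the H2 test could follow the hypothesis more closely: any coaching (160) against no in-home support (80) first, then Responsive against Structured, in fixed sequence. The first contrast has about 60 events (0.25 × 240) and detects a hazard ratio of exp(2.80/3.651) = 2.15 at the full .05. The price is giving up formal tests of each coaching format against no support unless they are added later in the sequence. The correction of the power text does not depend on this choice.

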### Data management

#### Confidentiality

Participants are assigned study identification numbers to link data across times. Confidentiality of individual responses is enhanced by removing additional information connecting to personal identities during data cleaning if present. Staff participants are instructed to avoid using names throughout focus group sessions. All electronic records of online consent are kept in a secure server maintained by research staff at the research institute and are kept separately from the data. Electronic data are encrypted and password protected. To minimize the risk that youth, caregivers, or staff could potentially be individually identified by an outside entity, data are not released to individuals not affiliated with the project, which is consistent with the CFR Protection of Human Subjects and related protections and regulations. Researchers with access to data are required to sign confidentiality statements. Any published reports by research staff only include aggregated data, so no individual person can be identified. All data use and access are governed by these regulations, policies, and procedures.

#### Data sharing

The current protocol is part of the Helping to End Addiction Long-term Prevention Initiative (NIH HEAL Prevention Initiative) with a total of 10 research institutes and 1 Coordinating Center [82]. All data are further de-identified (e.g., by systematically scrambling Study IDs within study sites) before being shared with the HEAL Prevention Coordinating Center. The Coordinating Center does not have access to identifying information, nor do they have access to or knowledge of how participant study identification numbers are scrambled. At project close, data will be shared publicly, following the HEAL Prevention Guidance for Appropriate Public Access and Data Sharing Plans. Sharing of underlying primary data for the publications will be made broadly available through an appropriate data repository, such as the NIH HEAL Initiative central data repository, or a non-NIH repository that conforms to the principles articulated in the HEAL Public Access and Data Sharing Policy [83].

#### Data safety and monitoring

The LeSA Project activities are governed by a Data Safety and Monitoring Board (DSMB) established by the funding agency and comprised of prevention scientists functioning independently of the funding agency. The DSMB meets with the research team semi-annually to ensure the safety of participants and the validity and integrity of the data. Adverse events are monitored by the research team and reported to the University IRB within 72 h of notification and severe adverse events are reported to the IRB and funding agency within 24 h of notification.

